**Discussion:**

The findings are expected to provide robust evidence regarding the efficacy and safety of opposing needling as an adjunctive therapy for KOA and to inform optimized treatment strategies.

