### Sample size

2.3

The sample size was estimated based on preliminary data (33, 34). The mean and standard deviation (SD) of the change in total WOMAC score after 8 weeks of treatment were assumed to be −32.3 ± 1.15 in the opposing needling plus electroacupuncture group, −22.42 ± 2.32 in the sham opposing needling plus electroacupuncture group, and −8.87 ± 0.81 in the conventional electroacupuncture group. The test power (1 − *β*) was set at 0.9, and the significance level (*α*) was set at 0.05. Based on these parameters, 30 participants were required per group. Considering a 20% dropout rate, the final sample size was determined to be 36 participants per group, resulting in a total of 108 participants.

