### Statistical analysis

2.12

Demographic Data Analysis: To assess the comparability between the three groups, demographic data and other baseline characteristics were compared. Continuous variables, such as age and Body Mass Index (BMI), were analyzed using independent-samples *t*-tests, provided that the data met the normality assumption. If the data did not meet the normality assumption, non-parametric tests, such as the Kruskal-Wallis test, were used. Categorical variables, such as gender, were analyzed using χ^2^ tests, ensuring that the assumptions for the test (e.g., adequate sample size in each category) were satisfied.

Clinical Efficacy Analysis: A multivariate analysis of covariance (ANCOVA) was performed to assess efficacy outcomes, with age, BMI, and disease duration included as covariates. The primary and secondary outcome measures were clearly defined, and potential confounding factors were controlled to ensure the robustness of the results.

Safety Analysis: The incidence of AEs and SAEs at 8 weeks post-randomization was compared across the three groups using χ^2^ tests. All AEs and SAEs were documented and analyzed to assess the safety of the interventions in each group.

Handling of Missing Data: After data collection is completed, the proportion, distribution, and possible mechanisms of missing data [e.g., missing completely at random (MCAR) or missing at random (MAR)] will be examined. For outcomes with a low proportion of missing data (≤5%) (36) and no apparent systematic pattern, complete-case analysis will be performed. If the proportion of missing data is higher or systematic missingness is observed, multiple imputation will be applied under the assumption of missing at random to reduce bias and maximize data utilization. Sensitivity analyses will be conducted to assess the robustness of the results under different missing data handling approaches. All analyses will be performed using R software (R version 4.4.3).

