## Discussion

3

The present study is expected to provide robust evidence regarding the efficacy and safety of combining opposing needling with electroacupuncture for KOA. By testing the hypothesis that this combination may produce additive or synergistic analgesic effects, the trial aims to elucidate the therapeutic value of integrating these two classical acupuncture techniques. A rigorous three-arm parallel-group design will be employed, including an OE group, a SE group, and an EA group. On one hand, this design allows for the evaluation of the additive effect of opposing needling as well as the overall therapeutic benefit of the combined intervention; on the other hand, both the OE and SE groups receive bilateral needling, which helps reduce the risk of unblinding. In addition, the trial incorporates a comprehensive set of outcome measures, enabling a multidimensional assessment of the therapeutic effects of opposing needling plus electroacupuncture. Finally, the study emphasizes standardization and reproducibility of the intervention: all treatments will be administered by uniformly trained acupuncturists, and quality control and monitoring procedures are established to ensure intervention consistency and internal validity of the results.

Nevertheless, certain limitations remain. The follow-up period is limited to 12 weeks, allowing only preliminary evaluation of efficacy and precluding assessment of long-term effects in KOA; future studies should consider extending the follow-up duration. In addition, this is a two-center study with a relatively small sample size. Larger and multicenter RCTs will be required to further validate the generalizability and external applicability of the findings.

Overall, the results of this study are expected to strengthen the clinical evidence for acupuncture-based management of KOA, inform treatment optimization, and provide a foundation for future research on innovative needling techniques in chronic pain management.

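### The three-group χ² test that is the only named safety comparison cannot, at 36 per arm, support the expected robust evidence on safety unless adverse events are common

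*Protocol article*

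**What the plan says.** The introduction gives safety as an aim alongside efficacy. The abstract states: "The findings are expected to provide robust evidence regarding the efficacy and safety of opposing needling as an adjunctive therapy for KOA". Section 3 repeats this for the combined treatment: "The present study is expected to provide robust evidence regarding the efficacy and safety of combining opposing needling with electroacupuncture for KOA".

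The method is in section 2.12: "The incidence of AEs and SAEs at 8 weeks post-randomization was compared across the three groups using χ^2^ tests". It is followed by: "All AEs and SAEs were documented and analyzed to assess the safety of the interventions in each group". That second sentence gives no estimate, interval or test.

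Section 2.3 derives the sample size from assumed WOMAC changes only. It says "30 participants were required per group" and then "the final sample size was determined to be 36 participants per group, resulting in a total of 108 participants". No expected AE rate, harm margin or detectable difference in AEs appears anywhere. Section 3 concedes a fairly small sample but links this to generalizability, not to safety.

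**The concern.** A test of no difference answers whether the data contradict equal risk. It does not say how large an excess risk the data still allow, and that is what a safety statement needs. If the test has little power, non-significance is the likely result whether or not the added treatment raises risk.

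The question is a real one here. OE adds penetrating needles at four points on the less affected side (section 2.6.1), three times a week for 24 sessions (section 2.6.6). SE uses non-penetrating devices on that side, and EA needles only the more affected side. Section 2.8 lists local pain, bleeding and bruising among the common events. The contrasts of interest are thus OE against SE and OE against EA. A 2-df test over three arms neither isolates nor estimates them.

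At stake is what the trial can say on one of its two stated aims.

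**Working it through.** **Inputs from the article.** Three arms, 1:1:1, 36 randomised per arm. This is 30 × 1.2 = 36, the stated 30 per group raised for the stated 20% dropout. The significance level of 0.05 is stated for the sample size. The article gives no power figure for safety, so there is none to reproduce.

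**Assumptions.** The alpha of 0.05 also applies to the safety test. SE and EA share a comparator AE proportion p, and OE has 2p. Because no rate is given, p is varied from 1% to 35%.

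**Step 1: the test.** With counts x₁, x₂, x₃ out of n per arm and p̄ = (x₁ + x₂ + x₃)/(3n),

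X² = Σ(xᵢ − n·p̄)² / [n·p̄(1 − p̄)],

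significant if X² > 5.99 (2 df).

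**Step 2: probability of missing a doubling.** The binomial probabilities were summed over all possible count triples that are not significant.

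| SE and EA rate | OE rate | Missed, n = 36 | Missed, n = 30 |
|---|---|---|---|
| 1% | 2% | 98% | 98% |
| 2% | 4% | 95% | 96% |
| 5% | 10% | 89% | 91% |
| 10% | 20% | 77% | 81% |
| 15% | 30% | 64% | 70% |
| 20% | 40% | 51% | 58% |
| 25% | 50% | 36% | 44% |
| 30% | 60% | 22% | 31% |
| 35% | 70% | 11% | 18% |

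The n = 30 column shows the case where only the pre-inflation number can be analysed.

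**Step 3: check by approximation.** For 10% against 20%, p̄ = (0.20 + 0.10 + 0.10)/3 = 0.1333. The noncentrality is 36 × [(0.0667)² + 2 × (0.0333)²] / (0.1333 × 0.8667) = 2.08. The noncentral χ² probability of falling below 5.99 is 77%, in agreement with the table.

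**Step 4: what a result would look like.** With 4/36 (11%) in both SE and EA:
- OE 10/36 gives p = 0.091.
- OE 11/36 (31%) gives p = 0.044, the first significant count.
- OE 7/36 (19%) gives p = 0.50, yet the 95% Newcombe interval for OE minus SE runs from −9 to +25 percentage points. The p-value alone hides that an excess of 25 points is still compatible with the data.

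**Step 5: serious events.** For an expected count of 5 per arm, 3 × 5 = 15 of the 108 participants would need a serious adverse event (SAE), so the χ² approximation is also doubtful for SAEs. If none occurs among 36, the one-sided 95% upper bound is 1 − 0.05^(1/36) = 0.080, or 8.0%.

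**Step 6: numbers needed.** For 80% power to detect a doubling between two arms, the requirement is 435 per arm at 5%, 199 at 10%, 82 at 20% and 42 at 30%.

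**The case against.** The strongest case against has four parts.

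*No rule equates non-significance with safety.* This stands. A reader might infer that the trial will present p ≥ 0.05 as proof that opposing needling is safe. The article says no such thing: it expects evidence regarding safety, which could be favourable or unfavourable, and it sets no equivalence or non-inferiority claim. What remains is narrower: the article states no other comparative safety output on which the expected robust evidence could rest.

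*The χ² test is not the whole safety analysis.* This stands in part. Section 2.12 adds an assessment in each group, and sections 2.8 and 2.9 require detailed recording of events. But no method is named for that assessment, and it is not described as a comparison.

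*The miss rates depend on an assumed AE rate.* This stands. A flat statement that the test misses a doubling 50% to 90% of the time holds only for comparator rates of about 5% to 20%. Over 24 sessions, with every AE recorded whatever its cause, the rate of any AE could be higher, and the test then does better: it misses 22% at 30% and 11% at 35%. For SAEs the rates are likely to be low, and there it does much worse.

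*Low power for AEs is usual, and intervals belong in an analysis plan.* Low power in a trial sized on efficacy is no fault in itself, and the absence of table-level detail from an article is no finding. The point is that two things that the article does state, an omnibus test as the comparison and a claim of robust safety evidence, do not fit each other at the stated sample size.

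**Conclusion.** The concern holds in a limited form. The article's one named between-group safety method cannot carry its claim of robust safety evidence, except where the AE in question is common.

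The size depends on the assumed comparator rate. For a doubling in OE only, at 36 per arm and alpha 0.05, the miss rate runs from 95% to 98% at 1% to 2%, through 89% at 5% and 51% at 20%, to 11% at 35%. For uncommon AEs and SAEs, a non-significant result carries little information on safety.

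The documents do not support the stronger conclusion that the trial will declare opposing needling safe on a non-significant p-value. Nor do they support a single miss rate. This is a cheap improvement worth making, not a defect in the trial's design.

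**What to change.** In section 2.12, make these the main safety output:
- the proportion with at least one AE, and with at least one SAE, in each arm with exact 95% confidence intervals;
- the OE-SE and OE-EA risk differences with 95% confidence intervals.

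Keep any test as supplementary, and state that non-significance will not be interpreted as evidence of safety or of equal risk.

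In the abstract and section 3, describe the safety data as descriptive instead of robust. Note there that no SAE among 36 would exclude only a rate above about 8% (one-sided 95% bound).

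The cost is wording in three places and a few lines of code. No further patients or data are needed. The intervals add no information to the 108 participants' data, but they show how much harm remains possible. The downside is a weaker safety claim.

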### Trial design

2.1

This is a three-armed RCT conducted at the Rehabilitation Department of the Thirteenth People’s Hospital of Chongqing and the Rehabilitation Department of Chengdu Pidu District Traditional Chinese Medicine Hospital. The total duration of the trial will be 12 weeks, comprising an 8-week intervention period followed by a 4-week follow-up period. A flow chart of the clinical trial procedure is presented in Figure 1, and the schedule of outcome measurements is detailed in Supplementary File 1 and Table 1.

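### The baseline t-test does not fit three arms, the adverse-event comparison and its scheduled assessment stop at week 8 of 12, and χ² is fixed for serious events without a check on counts

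*Protocol article*

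**What the plan says.** All three points are in section 2.12 of the protocol article, Statistical analysis.

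- **Baseline.** The stated aim is "To assess the comparability between the three groups, demographic data and other baseline characteristics were compared". For normally distributed data the text reads "Continuous variables, such as age and Body Mass Index (BMI), were analyzed using independent-samples" t-tests. Otherwise, "non-parametric tests, such as the Kruskal-Wallis test, were used". Categorical variables get χ², with a condition: "ensuring that the assumptions for the test (e.g., adequate sample size in each category) were satisfied".
- **Safety.** "The incidence of AEs and SAEs at 8 weeks post-randomization was compared across the three groups using" χ² tests. No condition on counts and no alternative test is given here. The next sentence has no time limit: "All AEs and SAEs were documented and analyzed to assess the safety of the interventions in each group".
- **Duration and schedule.** Section 2.1 describes 12 weeks, "comprising an 8-week intervention period followed by a 4-week follow-up period". Table 1 has one mark for adverse-event assessment, in the 8-week end-of-treatment column, and none at week 12. WOMAC, NRS and SF-36 are marked at week 12. Section 2.8 requires any adverse event to be recorded and promptly reported, whether or not it is related to the intervention.

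**The concern.** The baseline sentence cannot be carried out as written. A t-test gives no single comparison of three arms, and no pairwise scheme is described. The choice between t-test and Kruskal-Wallis, meant to depend only on normality, would also change the hypothesis being tested. If the sentence were carried out as three pairwise tests, chance imbalances would be flagged more often than the nominal level suggests.

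For safety, section 2.8 asks for every event, while the schedule and the between-arm comparison both stop when treatment ends. Events in the last four weeks would depend on unprompted reporting, and it is unclear whether they enter the comparison. The discussion promises robust evidence on safety as well as efficacy, so the safety window should be plain.

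χ² is a large-sample test. The authors attach a count condition to it for baseline categories but not for serious adverse events, where small counts are more likely.

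**Working it through.** **Inputs from the article.** Three arms, 1:1:1 (2.4); 36 per arm, 108 in total, and 30 per arm before the dropout allowance (2.3); 8 weeks of treatment plus 4 of follow-up (2.1). No adverse-event or serious-event rate is given, so the rates below are assumptions shown as a range. The article states no figure on this point that could be reproduced.

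**1. Baseline test.** One three-group test at 0.05 has a 5% false-positive rate per variable. For three pairwise t-tests at 0.05:
- if they were independent, the chance of at least one false positive is 1 − 0.95³ = 14.3%;
- they share arms, and simulation with 36 per arm (100,000 runs) gives 12.2%.

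**2. Safety window.** 12 − 8 = 4 weeks, and 4/12 is one third of planned observation. That third has a visit at week 12 but no adverse-event mark.

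**3. Expected counts.** The expected number of patients with an event, per arm, is n × pooled rate. Reaching 5 in each arm needs 15 patients with an event in total: a pooled rate of 5/36 = 13.9%, or 5/30 = 16.7% with 30 per arm.

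**4. Overall size of the nominal 5% Pearson χ² test**, 36 per arm, by full binomial enumeration:

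| Assumed pooled rate | Expected events per arm | True size |
|---|---|---|
| 1% | 0.36 | 0.8% |
| 2% | 0.72 | 2.5% |
| 5% | 1.8 | 3.7% |
| 10% | 3.6 | 4.6% |
| 20% | 7.2 | 5.2% |

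Averaged over possible event totals, the test is conservative at low rates.

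**5. Size given the observed total number of patients with an event**, 36 per arm:

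| Total | 1–2 | 3 | 4 | 5 | 6 | 7 | 8 |
|---|---|---|---|---|---|---|---|
| Rejection rate | 0% | 10.5% | 3.3% | 1.0% | 4.6% | 1.6% | 4.8% |

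**6. Two worked tables.**
- 3/0/0: the expected count is 1 per arm. χ² = (4 + 1 + 1) × (1/1 + 1/35) = 6.17 on 2 df, p = 0.046. The exact p is 3 × C(36,3)/C(108,3) = 3 × 7,140/204,156 = 0.105.
- 4/0/0: the expected count is 4/3 per arm. χ² = 8.31 on 2 df, p = 0.016. The exact p is 3 × C(36,4)/C(108,4) = 3 × 58,905/5,359,095 = 0.033. Both tests reject at 0.05.

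**The case against.** **On χ².** A reader might infer that χ² is anti-conservative for sparse safety data and will produce false safety signals. The calculations do not support that. The overall size is below 5% at every assumed rate up to 10%, and about 2.5% at a 2% rate. Among totals of 1 to 8, only 3 exceeds the nominal level, and with 4/0/0 both tests reach the same conclusion. Nor does the article call the events rare: it gives no rate, and section 2.8 describes the listed needling events as common. At about 14% incidence or more, χ² is acceptable. A condensed article may also leave a small-count alternative to the full protocol. What stands is narrower. The article fixes χ² by name for serious events, omits the condition it applies at baseline, and the test behaves erratically at small totals.

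**On the window.** A reader might infer that follow-up events are discarded. The documents do not say so. Week 8 is the end of treatment, and an on-treatment comparison is a recognised choice. Section 2.12 says that all events are analysed, and sections 2.8 and 2.9 set no cut-off for reporting. What stands is that the schedule has no week-12 entry and the only stated comparison ends at week 8, so the handling of weeks 9 to 12 is unclear.

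**On baseline.** The efficacy covariates (age, BMI and disease duration) are named in advance, so no efficacy estimate depends on baseline p-values. The article does not say that three pairwise tests will be run; the 12.2% holds only under that reading. The mismatch between the test and the number of arms remains.

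**Conclusion.** The point holds in a limited form.

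- **Baseline test:** wrong as written, with minor impact. It would matter only for how chance imbalances are described.
- **Safety window:** one third of the planned observation time has no scheduled adverse-event assessment and no stated between-arm comparison, although section 2.8 requires every event to be recorded. This is a gap in the schedule and an ambiguity in the analysis. It does not show that data will be lost.
- **χ² for safety:** unreliable when pooled incidence is below about 13.9% at 36 per arm. It is conservative on average there and exceeds its level at particular totals, most clearly three. This rests on the assumption that serious events, or some types of adverse event, will be infrequent.

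A general statement that the named tests do not fit the data would be supported for the t-test, and for χ² only if counts turn out small.

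**What to change.** 1. **Baseline (2.12).** Present baseline variables descriptively by arm, without tests. In a randomised trial, differences at baseline arise by chance and need no p-value. If a test is kept, name one-way ANOVA in place of the t-test, so that it matches Kruskal-Wallis.
2. **Schedule (Table 1).** Add an adverse-event mark at week 12.
3. **Safety window (2.12).** Report and compare adverse events and serious adverse events per arm from first treatment to week 12, and also split at week 8 so that the on-treatment picture is kept.
4. **Safety test (2.12).** Use the Fisher-Freeman-Halton exact test for serious adverse events and for infrequent types of adverse event. χ² can stay where expected counts are adequate.

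The cost is a few sentences and one adverse-event entry at a visit that already takes place. The exact test is slightly conservative. Sample size and efficacy analysis are unchanged.

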#### Withdrawal/dropout criteria

2.2.5

– Participants who are unable to tolerate acupuncture or fail to adhere to the designated study protocol;– Participants who develop severe joint inflammation during the study, characterized by significant swelling or moderate to large joint effusion;– Participants who experience other medical conditions requiring hospitalization, such as acute myocardial infarction or ischemic stroke.

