#### Management of withdrawal/dropout cases

2.2.6

– In the event of a participant dropout, the primary investigator should make efforts to contact the participant using methods such as home visits, phone calls, or letters to inquire about the reason for withdrawal. The date of the last treatment session should be recorded, and all feasible assessments should be completed.– For participants who withdraw due to adverse reactions or treatment failure, the primary investigator should provide appropriate treatment based on the participant’s specific condition.– Once a participant has been assigned a randomization number, they will be considered part of the study, regardless of subsequent changes in diagnosis or treatment completion.– All withdrawal/dropout cases will undergo intention-to-treat analysis after the study is completed.

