### Serious adverse events

2.9

SAEs include events that lead to hospitalization, prolongation of hospitalization, persistent or significant functional impairment, are life-threatening, result in death, or are considered by medical judgment to require intervention to prevent the occurrence of the above serious outcomes. In the event of an SAE, the clinical physician must immediately (within 2 h) report it to the project leader and the study team. The study team shall report the SAE to the ethics committee and the sponsor within 24 h. The SAE must be recorded in detail in the CRF, including the time of occurrence, severity, outcome, causal relationship, reporting status, and management process. Appropriate management should be implemented according to the participant’s condition, and consultation with relevant departments or hospitalization may be arranged if necessary. If emergency unblinding is required to confirm the treatment received, the participant will be withdrawn from the trial and recorded as a dropout. The study team will continue to follow up until the participant’s condition stabilizes. All costs arising from the management of SAEs and AEs will be covered by the study-designated funding.

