### Attendance and drop-out

2.10

Participants will be informed that they have the right to withdraw from the clinical trial at any time without obligation. The reasons for withdrawal will be tracked and recorded. Participants are not required to provide a reason for withdrawal; however, if the withdrawal is related to an AE, the investigator will take necessary measures based on the participant’s condition until it stabilizes. In the case of abnormal laboratory results, follow-up will continue until normalization is achieved. The method of follow-up, including hospitalization, outpatient visits, home visits, or telephone follow-up, will be determined based on the severity of the AE. Participants who receive other treatments or enroll in other clinical trials during the study will be considered as withdrawn from the trial.

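### Section 2.12 chooses the main missing-data method after the data are in and allows a complete-case analysis that conflicts with the intention-to-treat promise in 2.2.6, while 2.9 and 2.10 leave outcome collection after withdrawal unclear

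*Protocol article*

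**What the plan says.** Section 2.2.6 (Management of withdrawal/dropout cases) makes three commitments. Once participants have a randomisation number, "they will be considered part of the study, regardless of subsequent changes in diagnosis or treatment completion". After a dropout, "The date of the last treatment session should be recorded, and all feasible assessments should be completed". And "All withdrawal/dropout cases will undergo intention-to-treat analysis after the study is completed".

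Section 2.12 (Statistical analysis) settles the handling of missing data outcome by outcome once collection is finished. If no more than 5% is missing "and no apparent systematic pattern, complete-case analysis will be performed". If more is missing, or a systematic pattern is seen, multiple imputation under missing at random is used. Sensitivity analyses across missing-data approaches are planned.

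Three sections define who counts as withdrawn:

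- Section 2.2.5 includes "Participants who are unable to tolerate acupuncture or fail to adhere to the designated study protocol", as well as severe joint inflammation and hospitalisation for other conditions.
- Section 2.9 adds: "If emergency unblinding is required to confirm the treatment received, the participant will be withdrawn from the trial and recorded as a dropout".
- Section 2.10 adds: "Participants who receive other treatments or enroll in other clinical trials during the study will be considered as withdrawn from the trial".

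**The concern.** There are two linked problems.

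First, a complete-case analysis leaves out randomised participants whose outcome is missing, which is not what 2.2.6 promises. Which method becomes the main analysis is also decided after the missing data have been looked at, separately for each outcome. The condition on pattern has no stated criterion, and the 5% is not said to apply within each arm. Two analysts with the same data could reach different main analyses.

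Second, 2.9 and 2.10 say that certain participants are withdrawn from the trial, not merely from treatment. The follow-up described there is for safety: until the condition stabilises or laboratory values normalise. Neither section says whether WOMAC is still collected at the remaining visits. Emergency unblinding and seeking other treatment may be related to how the participant is doing. If outcomes are lost at these points, the loss could be outcome-related, whereas the main methods in 2.12 assume that it is not, or that observed data explain it.

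**Working it through.** **Inputs.** From 2.3: 30 per group required, 20% dropout, 36 per group, 108 in total; planned mean WOMAC changes of −32.3 (OE) and −22.42 (SE). From 2.12: the 5% threshold. Missing rates other than 20%, and all differences between missing and observed participants, are assumptions.

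**1. The plan's own figures.** 30 × 1.2 = 36 per group and 3 × 36 = 108, so the stated inflation is reproduced. (Dividing by 1 − 0.2 would give 37.5, that is 38; this is a separate matter.) Expected dropouts: 0.20 × 108 = 21.6. Planned OE–SE difference: 32.3 − 22.42 = 9.88 points.

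**2. How many participants the rule can omit.** Taking the proportion over all 108: 5/108 = 4.6% meets the threshold and 6/108 = 5.6% does not. The maximum is 5 per outcome. If all 5 are in one arm, that arm loses 5/36 = 13.9%.

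**3. How likely the complete-case route is.** With the number missing binomial (108, p), the chance of 5 or fewer is:

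| Missing rate p | P(≤5 missing) |
|---|---|
| 20% (planned dropout, if dropouts lack the outcome) | 0.000005 |
| 10% (assumed) | 0.035 |
| 5% (assumed) | 0.54 |
| 2% (assumed) | 0.98 |

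The route is in effect closed at the planned dropout. It becomes live if retention is much better than planned or if outcomes are collected after dropout.

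**4. Size when it applies.** Shift in an arm mean = share missing × (mean of missing − mean of observed). With all 5 in one arm and assumed differences of 5, 10 and 20 WOMAC points: 5/36 × 5 = 0.7; 5/36 × 10 = 1.4; 5/36 × 20 = 2.8 points. These compare with a planned OE–SE difference of 9.88. If two arms lose 2 and 1 participants, the net shift is 1/36 of the difference: 0.1, 0.3 and 0.6 points. Imputation would recover only the part that observed data explain.

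**5. Whether the pattern condition protects.** With 5 missing among three arms of 36 there are C(108,5) = 111,469,176 possible sets. A 5-0-0 split has exact p = 3 × 376,992 / 111,469,176 = 0.01. A 4-1-0 split or worse has p = 0.01 + 6 × 58,905 × 36 / 111,469,176 = 0.01 + 0.11 = 0.12. So 4 missing in one arm (11.1%) could pass as unsystematic; with an assumed 10- or 20-point difference that arm's mean moves by 4/36 × 10 = 1.1 or 4/36 × 20 = 2.2 points.

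**6. Withdrawal sections side by side.** Section 2.2.6 asks for all feasible assessments after dropout and analysis by intention to treat. Sections 2.9 and 2.10 say withdrawn from the trial and mention only safety follow-up. Neither refers back to 2.2.6, and 2.2.6 does not say whether the week 4, 8 and 12 WOMAC visits continue after these events. An investigator who reads 2.9 or 2.10 alone could reasonably stop collecting WOMAC.

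**The case against.** The strongest reply is that the plan already contains the safeguards. Complete-case analysis needs both a low proportion and no apparent pattern; if withdrawals visibly cluster, imputation applies even below 5%. Sensitivity analyses are planned. The rule is nearly inert at 20% dropout. Missing at random is a conventional main assumption, and its details belong in an analysis plan that is not shown. All of this stands and limits the size of the point. It does not remove the conflict between 2.2.6 and 2.12 or the data-dependent choice of the main analysis, both of which the article itself states. Step 5 also shows how weak the pattern condition is with five cases.

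Three stronger readings are tempting, and the documents do not support them.

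- A reader might infer that the plan removes from the analysis the cases most related to outcome. No section says so. Withdrawn and dropout are status labels, and 2.2.6 keeps these participants, asks for their assessments and analyses them.
- A reader might infer that the withdrawn are mostly treatment failures. Section 2.2.5 also lists hospitalisation for unrelated illness, and 2.10 includes joining another trial; the mix cannot be known in advance.
- A reader might attach a large bias to the plan by assuming both an imbalance in dropout between arms and a shift of the withdrawn from what imputation predicts. The documents give neither figure, and such a sum would measure the missing-at-random assumption, not the 5% rule.

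**Conclusion.** The point holds in limited form. Sections 2.2.6 and 2.12 contradict each other on whether every randomised participant is analysed, and 2.12 lets the observed data pick the main method without a criterion. The direct effect is small: at most 5 of 108 per outcome, and a worst-case shift in one arm of 0.7 to 2.8 points if the missing differ by an assumed 5 to 20 points. The route is very unlikely to be used if dropout is 20% and dropouts lack the outcome. Sections 2.9 and 2.10 do not fit 2.2.6 on assessment after withdrawal. The size of that gap cannot be computed from the documents, because it depends on how many participants are affected and on whether their outcomes are in fact collected. It is still worth correcting, because the change costs little and outcomes not collected at the time cannot be recovered.

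**What to change.** 1. In 2.12, replace the 5% rule with one pre-specified primary method for all randomised participants: either the multiple imputation already named, using all WOMAC visits (baseline and weeks 4, 8 and 12), or a likelihood-based repeated-measures model. Keep complete-case analysis as a sensitivity analysis only.
2. In 2.9 and 2.10, add a sentence that reconciles them with 2.2.6: after emergency unblinding, other treatment or enrolment in another trial, WOMAC assessments continue at the scheduled weeks unless consent is withdrawn, and the data are analysed in the randomised group. Rules on stopping treatment stay as they are.

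A sensitivity analysis that departs from missing at random is optional and can be left to the analysis plan.

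The cost is wording, slightly more analysis work, and some visits or calls of the kind 2.2.6 already foresees.
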